
### 2.5 Exploratory outcomes

In this trial, the exploratory outcomes will be as follows: 1) In the experimental and control groups, 30 cases will be randomly selected from patients who have had previous intracranial artery stenosis in the past, or at their current admission, to compare changes in blood vessel characteristics and plaques under high-resolution magnetic resonance (HR–MR) between the two groups after 180 days; 2) The magnetic resonance imaging (MRI) diffusion tensor imaging (DTI) anisotropy score, average diffusion rate, and diffusion tensor fiber bundle imaging will be compared between the two groups [30 cases will be randomly selected from each group; will be measured on D180]; 3) The proportion of patients with a good function status [defined as mRS score ≤2] will be measured on D180; 4) The distribution of the mRS scores will be measured on D180; 5) Motor function will be assessed by the FMMS score, which will measure its change from baseline at 180 days; 6) Cognitive function will be assessed by the MoCA score; its change from baseline will be measured on D180; 7) Recurrence rate of stroke [defined as cerebral infarction, cerebral hemorrhage] will be measured on D180; 8) The proportion of new combined vascular events [defined as ischemic stroke, hemorrhagic stroke, myocardial infarction, or vascular death] will be measured on D180.

### 2.6 Safety outcomes

The main safety outcome is the proportion of SAEs. Other safety outcomes include any adverse events (AEs) and clinically meaningful changes in vital signs or laboratory parameters during the study period.

### 2.7 Follow-up procedures

The study will consist of four visits, including time of randomization (baseline) and 30, 90, and 180 days after randomization. At baseline, we will evaluate demographic characteristics; routine laboratory test results; computed tomography (CT)/MRI results; electrocardiogram (ECG) results; and NIHSS, Alberta Stroke Program Early CT Score (ASPECTS) (Barber et al., 2000), mRS, FMMS, MoCA, BI and EQ-5D scores. Stroke types will be classified according to the trial of ORG 10172 in acute stroke treatment (TOAST) criteria. At 30, 90, and 180 days after randomization, we will perform assessments using the mRS, NIHSS, FMMS, MoCA, BI and EQ-5D scores. Vital signs and physical examination findings will be recorded at both baseline and 90 days. Finally, medication use for comorbidities and adverse events information will be recorded at whenever they occur during the trial.

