## 2 Methods and design

### 2.1 Study design and patient selection

The LONGAN trial is a prospective, multicenter, randomized, placebo-controlled, double-blind, parallel-group, superiority trial that enrolls patients from stroke and rehabilitation units in China. This study will be conducted at 15 sites across China. The primary objective of the trial is to test the hypothesis that LSZ capsule is superior to the placebo for increasing the proportion of favorable functional status, defined as a modified Rankin Scale (mRS) score ≤1 at 90 days. The secondary objective is the assessment of any other benefits or harms from the end of the treatment period up to 180 days after the stroke. Participants will be followed up at 30, 90 and 180 days after randomization (D30, D90 and D180, respectively) to collect efficacy and safety outcomes in person. Patient enrollment will begin in May 2022 and end in June 2023. Figure 1 presents a schematic diagram of the patient timeline. The trial was approved by the institutional review board of Dongzhimen Hospital, Beijing University of Chinese Medicine, Beijing, China and registered in public clinical trial database (No. 2021DZMEC-198-02; ClinicalTrials.gov Identifier NCT 05277311). We described this study protocol according to the SPIRIT 2013 Statement, and the complete checklist is available.

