### 2.3 Treatment

Eligible patients will be randomly assigned to the experimental and control groups. Participants in the experimental group will receive 5 LSZ capsule (0.4 g each), three times a day for 90 days. The control group will receive a LSZ placebo using the aforementioned protocol; the main ingredients of placebo including starch, dextrins, silicon dioxide, medical yellow iron oxide, caramel color liquid, and purified water will be identical to the LSZ capsule in appearance, weight, and taste. The treatment assignments are presented in Figure 2. All patients will receive a standard treatment, which is referred to in the current guidelines (Chinese Society of Neurology and Chinese Stroke Society, 2018; Powers et al., 2019), including antiplatelet therapy, control of vascular risk factors, and appropriate rehabilitation. During the trial, drugs with composition or efficacy similar to the study drug, such as CM decoctions (compound granules), CM injections, and Chinese patent medicine and health products, will not be permissible. Other concomitant medications will be allowed during the study, but these should be recorded in the subjects’ CRF during the trial. The study drug will be discontinued in cases of SAEs, request for study withdrawal by the patient or their legally authorized representative, or poor compliance or non-adherence to the prescribed interventions. We will truthfully record the reasons for stopping interventions.

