#### 2.12.6 Analysis of safety outcomes

Based on the SS data set, the method of statistical description will be used, and the differences in the incidence of primary and secondary safety endpoints will be compared between the two groups. For most safety endpoints, HR values between the two treatment regimens will be calculated using Cox proportional hazards models; Poisson regression or negative binomial regression will be used for rare events. AEs and SAEs will be listed separately, and a summary analysis will be performed. Within each treatment group, the number and proportion of AE cases will be aggregated separately by tissue system classification and by items of interest. In addition, all deaths and SAEs will be described in detail using case narratives.

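### Vital-sign change is a safety outcome for the whole study period, but the article schedules only one post-baseline reading, at D90

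*Protocol article*

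**What the plan says.** Section 2.6 of the protocol article names SAEs as the main safety outcome. Among the other safety outcomes, separately from adverse events, it lists "clinically meaningful changes in vital signs or laboratory parameters during the study period".

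Section 2.1 describes follow-up at "D30, D90 and D180, respectively) to collect efficacy and safety outcomes in person". Section 2.7 confirms the visit plan: "The study will consist of four visits, including time of randomization (baseline) and 30, 90, and 180 days after randomization". It then says what is done at the post-baseline visits: "At 30, 90, and 180 days after randomization, we will perform assessments using the mRS, NIHSS, FMMS, MoCA, BI and EQ-5D scores". Vital signs have their own sentence: "Vital signs and physical examination findings will be recorded at both baseline and 90 days". The same section adds that "adverse events information will be recorded at whenever they occur during the trial".

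Treatment is given "three times a day for 90 days" (Section 2.3).

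On analysis, Section 2.12.6 plans statistical description and a comparison of incidence between the arms. It continues: "For most safety endpoints, HR values between the two treatment regimens will be calculated using Cox proportional hazards models". Poisson or negative binomial regression is kept for rare events. The section does not name vital signs.

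**The concern.** The outcome is defined over the study period, which runs to D180, but its scheduled measurement is a single reading on the last day of treatment. A comparison built on that reading describes the state of patients at D90. It does not describe what happened to vital signs during the course, or after it. Section 2.6 lists vital-sign change apart from adverse events, which suggests a measured outcome and not one that depends on spontaneous reporting.

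What is at stake is one secondary safety comparison. If the arms look alike at D90, a reader may take this as evidence of no vital-sign effect over the study, and the schedule cannot support that. The analysis is also left open. Most safety endpoints are to get a hazard ratio, and it is not stated whether an outcome read at a single visit is one of them.

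**Working it through.** The article states no figure for this outcome, so there is nothing to reproduce. The check is a comparison of the sections, followed by a short calculation on the Cox model.

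**Step 1: the schedule against the definition**

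| Visit | Safety outcomes collected (2.1) | Vital signs scheduled (2.7) | Treatment status (2.3) |
|---|---|---|---|
| Baseline | – | yes | start |
| D30 | yes | not listed | in course |
| D90 | yes | yes | end of course |
| D180 | yes | not listed | 90 days after end of course |

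Scheduled post-baseline readings: 1 of 3 visits. There is none after baseline until D90, so none inside the 90-day course before its end. There is none from D90 to D180, an interval of 180 − 90 = 90 days, which is half of the follow-up.

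**Step 2: what else could catch a change**

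Section 2.7 records adverse events when they occur. Section 2.10 includes those found on physical or laboratory examination. A change outside D90 can therefore reach the data, but only if somebody measures it, judges it to be an adverse event and reports it. This is not a systematic measurement with a known denominator.

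**Step 3: what a Cox model would give if applied to D90-only readings**

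Let arm 1 have d₁ events among n₁ patients and arm 0 have d₀ among n₀, all at one common time. The Breslow partial likelihood is

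L(β) = exp(β·d₁) / (n₀ + n₁·exp(β))^(d₀ + d₁).

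Setting the score to zero gives d₁·n₀ = d₀·n₁·exp(β), so

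exp(β) = (d₁/n₁) / (d₀/n₀),

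which is the risk ratio.

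The article gives no event rates, so these numbers are assumed for illustration: 93/619 against 62/619 (about 15% against 10%), with 619 per arm from 1,238/2 in Section 2.11.

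- Breslow ties: hazard ratio (93/619)/(62/619) = 1.50, equal to the risk ratio.
- Efron ties: hazard ratio 1.54 from the model fit.
- Odds ratio: (93/526)/(62/557) = 1.59.

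The hazard ratio can be computed, but it moves with the handling of ties and says nothing about timing beyond the two D90 proportions.

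**The case against.** The strongest reply has four parts.

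- **No express limit.** Section 2.7 does not say that vital signs are taken at no other time. The timeline in Figure 1 is not shown, and the article condenses a fuller protocol. This is fair: the absence of D30 and D180 readings is the natural reading, not an express exclusion. But the article does state a schedule, so the point rests on what it says and not on silence.
- **Section 2.1 is general.** It does not promise every outcome at every visit. Among the secondary outcomes in Section 2.4, motor and cognitive change are defined at D90 only, while others are defined at D30 and D90. A change from baseline to D90 also falls within the study period. This stands, and it makes the matter a mismatch to reconcile, not a flat contradiction. It does not supply the missing readings.
- **Adverse events are captured continuously.** A reader might infer that every change before D90 is missed. Sections 2.7 and 2.10 do not support that, because a change that is noticed can be recorded when it happens. What is lost is systematic measurement.
- **Cox is planned for most endpoints, not all.** A reader might infer that the plan assigns vital signs to a Cox model. It does not. Section 2.12.6 also plans a comparison of incidence, which would suit a D90 proportion. The Cox remark is therefore conditional.

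**Conclusion.** The point holds as a modest one that is cheap to correct. The stated schedule measures a named safety outcome once after baseline, at 1 of 3 visits, while the definition covers the whole study period. This rests on reading the vital-sign sentence in Section 2.7 as the complete schedule. If the full protocol has more readings, the article's sentence still needs correcting.

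Two further inferences are tempting but not supported.

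- **Bias from early stopping.** One might argue that stopping treatment removes affected patients and pulls the comparison towards no difference. Section 2.2 says that patients who stop early are still followed. They may be off drug at D90, but they are not removed. The article gives nothing on the direction of any bias.
- **Loss of power.** With assumed event rates and an assumed share caught at D90, a fall in power can be calculated. Neither assumption has a source in the article, and the trial is not sized on this outcome. Such a figure would not show a defect in the plan.

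The primary outcome, the main safety outcome and the sample size do not depend on this point.

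**What to change.** Reconcile Sections 2.1, 2.6 and 2.7 in one of two ways.

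1. **Measure what is defined.** Record vital signs at D30 and D180 as well as D90. Count a patient as having the treatment-period outcome if a clinically meaningful change is seen at D30 or D90, and report D180 separately as the period after treatment. Patients already attend these visits in person, so the cost is a few minutes per visit and one CRF page.
2. **Define what is measured.** Keep the present schedule and restate the outcome as clinically meaningful change from baseline at D90. This costs wording only, but it gives up the earlier and later periods.

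In either case, state in Section 2.12.6 that this visit-based outcome is compared as a proportion, with a risk difference or risk ratio and its 95% confidence interval. Say there which safety endpoints receive a time-to-event analysis.

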### 2.8 Data collection and management

Data collection and management will be conducted in collaboration with clinicians and clinical research coordinators. All researchers responsible for patient recruitment, results evaluation, and data collection will receive standardized training on the standard operating procedures of this trial prior to patient recruitment. During the pilot study, there will be personnel responsible for follow-ups. Patient information will be recorded by the investigator in the patients’ CRF. Subsequently, the clinical research coordinator will use the unique login identity document (ID) to enter the data into the electronic CRF. All patient-related information will be stored in a locked file cabinet in the medical center with limited access rights. All reports, data collection, and administrative forms will be identified by coded ID numbers to protect the confidentiality of participants.

### 2.9 Quality control and data monitoring

The steering committee will be responsible for the scientific content of the protocol, supervision of research operations, the internal data sharing process, and preparation of preliminary manuscripts and other publications produced by the study. Quality control will be applied at every stage of data processing to ensure that all data is reliable and processed correctly. A Data and Safety Monitoring Board (DSMB), whose members are independent of the researchers and steering committee, will periodically evaluate the progress of the clinical trials, safety data, and clinical efficacy endpoints. A mid-term efficacy analysis is planned. After recruiting 50% of patients, a DSMB report should be prepared. If considered necessary, DSMB can request additional reports. If an unexpected safety issue arises or a treatment difference is found during a pre-specified interim analysis, DSMB is responsible for recommending early termination of the study. Two contract research organizations will regularly monitor data and conduct data quality control. Data analysis will be completed by a third-party statistical unit (Beijing Tiantan Hospital, Capital Medical University, Beijing, China). An auditing will be conducted twice a month during the enrollment period and every month during the follow-up period, and the process will be conducted without the involvement of investigators and the sponsor.

### 2.10 Adverse events management

All information about AEs mentioned by the subject, discovered by the investigator, or discovered through physical examination, laboratory examination, or other methods, should be recorded on the adverse event page of the CRF, managed in accordance with corresponding regulations, and reported. Subsequently, the patient will be treated, the treatment outcome will be recorded, and they will be followed up until they recover or stabilize. The investigator will report any SAEs to the ethics committee, contract research agency, chief investigator, and the China Food and Drug Administration.

### 2.11 Sample size calculations and interim analysis

The 90-days mRS distribution of the eligible population in The Third China National Stroke Registry (CNSR-Ⅲ) indicates that the proportion of mRS ≤1 is 60.42% (Wang et al., 2019). This study assumes that the proportion of patients with mRS ≤1 in the control group will be 60%, and the proportion of patients with mRS ≤1 in the experimental group will be increased by approximately 15% for a proportion of 69%. According to this assumption and calculations using PASS 11.0 software (NCSS, LLC, East Kaysville, UT, United States), a total sample size of 1,238 in the two groups can achieve 90% power and rule out two-sided type I errors of 5% to detect a superiority margin difference of 5% in this two-arm trial, with an allocation ratio of 1:1. With an estimated loss-to-follow-up rate of 10%, a total of 1,376 participants will be recruited. An interim analysis will be performed when the 50% of recruited patients (619) complete the study. The interim analysis will allow the DSMB to decide whether to continue or terminate the study. Based on the existing data and the expected final sample size, if this study is not expected to obtain efficacious results, the study will be terminated immediately in the current period. For evaluation of the effectiveness of the research, if the research has met the validity standard and meets the requirements of the inspection level, the study can be terminated early. The study will continue if the estimated efficacy is expected to be achieved by the end of the study. If the estimates of the primary outcome in the study (blinded) differ significantly from the actual values, the final sample size allows for appropriate adjustments at the interim analysis.

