#### 2.12.4 Analysis of the primary outcome

The primary outcome, the proportion of patients with favorable outcome in each group, will be compared by the chi-square test. Assessment of the primary effect will involve the analysis of differences in mRS scores between the LSZ treatment and placebo groups using ordinal logistic regression; the results will be expressed as odds ratios (ORs) with 95% confidence intervals (CIs). Both covariate-adjusted analysis and covariate-unadjusted analysis will be performed. Adjusted analyses will incorporate the following covariates: age, sex, baseline National Institutes of Health Stroke Scale (NIHSS) score, TOAST classification. Adjusting for prognostic factors enhances statistical power in clinical trials, which can also correct for imbalances in baseline prognostic variables, reducing data variability (Optimising the Analysis of Stroke Trials (OAST) Collaboration et al., 2009; Kahan et al., 2014).

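### The stated 5% superiority margin does not fit the sample size: 1,238 patients give about 31% power against it, and 90% only if the margin is zero

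*Protocol article*

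**What the plan says.** All the sample size inputs are in section 2.11 of the protocol article.

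- Control rate: the plan assumes that "the proportion of patients with mRS ≤1 in the control group will be 60" per cent.
- Experimental rate: the proportion "in the experimental group will be increased by approximately 15% for a proportion of 69" per cent. The 15% is relative (60% × 1.15 = 69%), so the absolute difference is 9 points.
- Error rates and margin: 1,238 patients in total "can achieve 90% power and rule out two-sided type I errors of 5% to detect a superiority margin difference of 5" per cent, "with an allocation ratio of 1:1".
- A 10% loss to follow-up raises the total to 1,376.

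No other section mentions a margin. Section 2.1 sets out a plain hypothesis of superiority over placebo. Section 2.12.4 says the proportions with a favourable outcome "will be compared by the chi-square test". Section 2.12.5 sets a two-sided 5% significance level for all tests.

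**The concern.** A superiority margin is a technical term. It moves the null hypothesis from no difference to a benefit no larger than the margin, so the lower confidence limit must exceed the margin for the trial to succeed. Here the margin takes up more than half of the assumed effect, and a sample sized for 90% power on the whole 9 points cannot keep that power on the remaining 4. Nor can the 5% be read as another name for the effect size, because the same paragraph gives the effect as 9 points absolute and 15% relative.

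Two things are at stake. The power claim is false for the criterion as worded. And a result whose 95% lower confidence limit falls between 0 and 5 points would pass the chi-square test but fail the stated margin. The interim rules in section 2.11, which let the monitoring board stop for efficacy or for lack of it, also depend on which null applies.

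**Working it through.** **Inputs (section 2.11):** p₁ = 0.60, p₂ = 0.69, difference 0.09, two-sided α = 0.05 (z = 1.960), power 90% (z = 1.2816), 1:1 allocation, 1,238 / 2 = 619 per arm. The scale of the 5% is not stated; it is read first as 5 percentage points.

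**1. The plan's figure with a zero margin**

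Pooled two-proportion formula, with mean rate 0.645:

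n = [1.960 × √(2 × 0.645 × 0.355) + 1.2816 × √(0.24 + 0.2139)]² / 0.09² = 592 per arm, or 1,184 in total.

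With continuity correction: 614 per arm, or 1,228 in total. That is within 1% of 1,238.

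Power at 619 per arm: 91.2% uncorrected. With the continuity correction (subtract 1/619 from the difference) it is 90.2%.

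Loss to follow-up: 1,238 / 0.9 = 1,376, as stated.

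**2. The stated figure with a 5-point margin**

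Standard error = √(0.4539 / 619) = 0.0271.

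Power = Φ[(0.09 − 0.05) / 0.0271 − 1.960] = Φ(−0.48) = 31.5%.

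The choice of variance hardly matters: 31.2% with the pooled variance, 31.3% with the Farrington–Manning variance. If all 1,376 patients were evaluable (688 per arm), power would be 34%. At one-sided 5% instead of 2.5%, 619 per arm give 43%.

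Size for 90% power: (1.960 + 1.2816)² × 0.4539 / 0.04² = 2,981 per arm, or 5,962 in total. That is 5,962 / 1,238 = 4.8 times the stated size.

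**3. Other readings of the 5%**

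| Reading | Power at 619 per arm | Per arm for 90% |
|---|---|---|
| Zero margin, 60% v 69% | 91% | 592 (614 corrected) |
| Margin of 5 points | 31% | 2,981 |
| Relative margin of 5% (3 points) | 60% | 1,325 |
| True difference of 5 points (60% v 65%) | 44% | 1,969 |

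Only the zero-margin row agrees with 1,238 patients and 90% power.

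**4. What each criterion demands of the data**

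1.960 × 0.0271 = 0.053. Success against zero needs an observed difference of about 5.3 points. Success against a 5-point margin needs about 5 + 5.3 = 10.3 points, more than the 9 points assumed. If the true rates are 60% and 69%, the chance that the result falls between the two thresholds is about 91.2% − 31.5% ≈ 60%.

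**The case against.** The strongest reply is that this is a slip of wording and not a design fault. Without the margin phrase the paragraph is coherent: 60% and 69% agree with a 15% relative increase, 1,238 gives 90% power, and the allowance for loss is right. The hypothesis, the primary test and the significance level all point to a null of zero, and no section gives a decision rule that uses 5 points. On that view the success criterion is settled elsewhere and the trial is adequately powered.

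Most of this stands. The margin wording is the probable error, and nothing here shows that the trial is too small for the test it plans. But the sentence makes a specific technical claim that no reading of the 5% supports, in an article that presents itself as the public pre-specification. A reader should not have to infer from other sections that the sentence must be ignored.

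A smaller point is that neither 1,184 nor 1,228 equals 1,238, so the exact route to the number is not established. An allowance for the interim look could close the gap: if an O'Brien–Fleming boundary with an inflation factor of about 1.007 is assumed (the article names none), 614 × 1.007 = 618.3, which rounds up to 619 per arm. The conclusion does not depend on this.

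**Conclusion.** The concern holds. Section 2.11 claims 90% power against a 5% superiority margin, but at the stated rates and size the power against 5 points is about 31%. It rises to 43% at one-sided 5%, and to 60% if the margin is taken as relative at two-sided 5%. The sample size fits a test of no difference, where power is 90% to 91%. These results take the assumed 60% and 69% as true and use normal approximations; the variance method changes the 31% by less than half a point. The likely fault is the margin phrase and not the number of patients, but as published the power statement is wrong and must be corrected.

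**What to change.** Delete the margin phrase from section 2.11. State instead that the null hypothesis is a difference of zero, that the assumed rates are 60% and 69% (9 points absolute, 15% relative), and that 1,238 evaluable patients give about 91% power at two-sided 5% for the uncorrected chi-square test (about 90% with continuity correction). This changes one sentence. It needs no extra patients and no change to the primary test.

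If the sponsor does intend a 5-point margin, three changes are needed: give its scale and justification; replace the primary test with a comparison of the lower 95% confidence limit against 5 points; and either restate power as about 31% or resize to about 5,962 evaluable patients (5,962 / 0.9 ≈ 6,625 recruited at 10% loss). The interim criteria should refer to the same null.

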#### 2.12.5 Analysis of the secondary and exploratory outcomes

For dichotomous outcomes, including the proportion of patients of good functional status (mRS ≤2), the proportion of poor-HRQOL (EQ-5D index score ≤0.5), the proportion of patients with functional independence (BI ≥ 90), the distribution of mRS scores, recurrence rates of stroke, and the proportion of new combined vascular events, a comparison of how patients with these outcomes are distributed among the two groups will be assessed using a chi-square test or Fisher’s exact test and presented as OR estimates and 95% CIs using logistic regression. Moreover, the distribution of functional outcomes on the mRS in both groups will be expressed in histograms. For other secondary outcomes of continuous variable, the changes from baseline to the endpoint of treatment for the above outcomes, including neurological deficit, motor function and cognitive function will be analyzed using the Student’s t test or Wilcoxon rank-sum test where appropriate. For survival data, the Kaplan-Meier method will be used to estimate the survival rate of each group; a survival curve will be drawn, and the log-rank test will be used to evaluate the curative effect. Cox proportional hazards models will be used to calculate hazard ratios (HR) and 95% CIs between the two treatment regimens. The central effect will be set as a random effect in all models. All statistics will be evaluated using two-sided tests, and *p* < 0.05 will be considered statistically significant.

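### The interim analysis allows an efficacy stop, but the only significance level stated is two-sided 0.05 for every test, so the 5% type I error claimed in section 2.11 is not kept as written

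*Protocol article*

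**What the plan says.** All references are to the Protocol article.

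- Section 2.9: "A mid-term efficacy analysis is planned". A treatment difference found at a pre-specified interim analysis is a ground on which the DSMB recommends early termination.
- Section 2.11: the interim takes place when 619 patients have completed. On efficacy, "if the research has met the validity standard and meets the requirements of the inspection level, the study can be terminated early". No number is attached to that level.
- Section 2.11, sample size: 1,238 patients "can achieve 90% power and rule out two-sided type I errors of 5"%, for 60% against 69% with mRS ≤1.
- Section 2.12.4: the primary proportion is compared by a chi-square test. No significance level is given there.
- Section 2.12.5, last sentence: all statistics are tested two-sided, and p < "0.05 will be considered statistically significant".

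No other significance level, stopping boundary, spending function or reduced final level appears in the document.

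**The concern.** A trial that may claim success at an interim look and again at the end has two opportunities for a false positive. Keeping the overall error at 5% means that alpha used at the interim must be taken from the final test. The article fixes the final test at 0.05 by a rule covering every statistic, permits an efficacy stop before it, and still claims 5% overall.

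The single confirmatory claim of the trial rests on this. If the interim level is settled only after by-arm results have been seen, it is no longer pre-specified, and neither an early stop nor a final p-value just under 0.05 can be taken at face value.

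**Working it through.** **Inputs.** Section 2.11: 60% against 69%, 90% power, two-sided 5%, 1:1 allocation, 1,238 evaluable, 10% loss, 1,376 recruited, interim at 619 completers. Section 2.12.5: p < 0.05. The document gives no interim level, so several standard levels are assumed below to show the range.

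**The plan's own sample size.** With d = 0.09, mean rate 0.645 and variance sum 0.60×0.40 + 0.69×0.31 = 0.4539:

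n = [1.96×√(2×0.645×0.355) + 1.2816×√0.4539]² / 0.09² = 592 per arm (1,184 in total).

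With the continuity correction, (n/4)×[1 + √(1 + 4/(n×d))]² = 614 per arm (1,228), within 1% of the stated 1,238. The dropout step is exact: 1,238/0.90 = 1,375.6, rounded up to 1,376.

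**Information fraction.** 619/1,238 = 0.50. If all 1,376 were analysed, it would be 619/1,376 = 0.45.

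**Overall type I error.** Under the null, the interim statistic Z1 and final statistic Z2 are bivariate standard normal with correlation √0.5 = 0.707. The overall two-sided error is P(|Z1| > c1 or |Z2| > c2). The final cut-off is c2 = 1.96, because 0.05 is the only level stated. No credit is taken for futility stopping.

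| Interim level (assumed) | c1 | Overall error, final test at 0.05 |
|---|---|---|
| 0.001 (Haybittle-Peto) | 3.291 | 5.02% |
| 0.0031 (Lan-DeMets O'Brien-Fleming-type) | 2.963 | 5.1% |
| 0.0052 (O'Brien-Fleming) | 2.797 | 5.2% |
| 0.0294 (Pocock) | 2.178 | 6.7% |
| 0.05 (section 2.12.5 taken literally) | 1.960 | 8.3% |

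For the last row, the two looks each have a 5% chance of rejecting and a 1.69% chance of both rejecting: 5% + 5% − 1.69% = 8.31%. A binomial simulation with both arms at 60% (1,000,000 trials) gave 8.4%. At an information fraction of 0.45 the figure is 8.5%.

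**Levels that restore 5%, one example.** Lan-DeMets O'Brien-Fleming-type spending at t = 0.5 spends, per side, 2×[1 − Φ(2.2414/√0.5)] = 0.00153. This gives c1 = 2.963 (two-sided p = 0.0031). Solving for an overall 5% gives c2 = 1.9686 (p = 0.0490).

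**Power at 619 per arm.** Standard error = √(0.4539/619) = 0.02708, so the expected final Z is 0.09/0.02708 = 3.324. Fixed design: Φ(3.324 − 1.960) = 91.4%. With the spending rule above: 91.3%. (Using the pooled variance under the null, fixed-design power is 91.2%.)

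**The case against.** **The boundary may sit in a fuller document.** The article calls itself a summary, and a stopping boundary is commonly left to a full analysis plan or DSMB charter. That stands as far as it goes: the missing boundary alone would not be a finding. What remains is a conflict in stated text, because the article does fix a level, 0.05 for all statistics, next to a permitted efficacy stop and a 5% claim.

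**The p < 0.05 sentence closes a section on secondary and exploratory outcomes.** It could be read as a general default. But it covers all statistics, and the primary analysis section offers nothing else.

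**Nothing says the interim is tested at 0.05.** Correct. The 8.3% is the literal-reading upper case for one interim look. A strict unstated interim level would leave an excess of only 0.02 to 0.2 points.

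**A binding futility rule could offset a small excess.** This is possible. With an assumed conditional-power cut-off of 20% under the current trend, the superiority-side error would be 2.1% with an O'Brien-Fleming interim, but 3.7% with an interim at 0.05, against 2.5%. No threshold is stated, so no credit can be taken.

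A reader might also infer three stronger points that the document does not support:

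- *That the sample size ignores the interim look.* The calculation names no look, but the arithmetic does not settle it: 614 per arm times the O'Brien-Fleming inflation of 1.007 is 618.4, hence 619 per arm, or exactly 1,238.
- *That there will be three or more efficacy tests.* Section 2.9 says "If considered necessary, DSMB can request additional reports", but does not say that such reports carry an efficacy test or permit an efficacy stop.
- *That the futility rule costs power.* The wording is firm ("if this study is not expected to obtain efficacious results, the study will be terminated immediately in the current period"), but section 2.11 also leaves the decision to the DSMB. Any power loss depends on a threshold that the article may properly leave elsewhere.

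Nor is the sample size adjustment at the interim a further defect here, since section 2.11 already marks the estimates used for it as blinded.

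**Conclusion.** The point holds as a conflict between sections 2.9 and 2.11 (efficacy stop allowed, 5% error claimed) and section 2.12.5 (0.05 for everything). The excess over 5% runs from about 0.02 to 3.3 percentage points, and where it falls depends entirely on the interim level that the document does not give.

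This assumes one efficacy look at 50% information, a final primary test at 0.05 and no credit for futility stopping. It does not depend on how 1,238 was derived. Because the two levels define what counts as success on the primary outcome, and lose their value if set after by-arm data are seen, this must be fixed before the interim.

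**What to change.** Before any by-arm interim data are seen:

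1. In section 2.11, state the interim efficacy level for the primary outcome (mRS ≤1 at D90) and the matching final level. One valid choice is Lan-DeMets O'Brien-Fleming-type spending: two-sided p < 0.0031 at 50% information and p < 0.0490 at the end. Say that both will be recomputed for the actual information fraction and for any added efficacy look. Other boundaries that keep 5% overall would also serve, such as 0.001 and 0.0498 (Haybittle-Peto) or 0.0052 and 0.0480 (O'Brien-Fleming).
2. In section 2.12.5, exempt the primary test from the general p < 0.05 sentence, and refer to the final level from section 2.11 in section 2.12.4.
3. In section 2.11, say whether 1,238 already allows for the interim look.

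The cost is wording in the plan and the DSMB charter. With the first choice, the final level falls from 0.050 to 0.049 and power at 619 per arm from 91.4% to 91.3%, still above the planned 90%, so no extra patients are needed. A Pocock boundary would cost more: its inflation factor is 1.100, which takes 614 per arm to 676, or 1,352 evaluable patients.
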